## Abstract

Background: Women with fibromyalgia (FM) have 2.5 falls per year compared to the 0.5 falls in people without FM. This fact poses a significant health expense. Square Stepping Exercise (SSE) is a balance training system that has been shown to be effective in preventing falls in the elderly. However, there are neither studies in people with FM nor studies that apply SSE through video-conferencing (Tele-SSE). The objectives of this project are 1) to investigate the applicability, safety, decrease in the number of falls, and incremental cost-effectiveness ratio of prevention of falls program through Tele-SSE in women with FM, and 2) to study the transfer of obtained results to the public and private socio-health economy of Extremadura. Methods/Design: A randomized controlled trial with experimental (Tele-SSE) and control (usual treatment) groups will be carried out. The application of Tele-SSE will be performed for 12 months (three times per week) and one additional follow-up month after the intervention. A focus group including agents to identify key points to transfer the findings to the public and private sectors in Extremadura. One-hundred and eighteen women with FM will be recruited and randomly distributed into the two groups: Experimental (Tele-SSE; *n* = 59) and control group (Usual care; *n* = 59). Primary outcome measures will be: 1) Applicability; 2) safety; 3) annual number of falls; and 4) incremental cost-effectiveness ratio. Secondary outcomes will be: 1) Balance; 2) fear of falling; 3) socio-demographic and clinical information; 4) body composition; 5) physical fitness; 6) physical activity and sedentary behavior; 7) quality of life-related to health, mental health, and positive health; 8) pain; 9) disability level; 10) cognitive aspects; and 11) depressive symptoms. Regarding the focus group, the acceptability of the Tele-SSE will be evaluated in social-sanitary agents and will include Tele-SSE in their services offer. A statistical analysis will be carried out by treatment intention and protocol. In addition, a cost-effectiveness analysis from the perspective of the health system will be performed. Discussion: This project aims to improve the efficiency and equity of physical therapy services based on tele-exercise in preventing falls in people with FM. Furthermore, orientations will be given in order to transfer the obtained findings into the social-sanitary system and market.

## 1. Background

Falls are a major cause of injury and premature death in older people [1]. These falls can cause fractures that negatively affect the quality of life of this population [2], which can pose a great economic expense for public health. For instance, the medical cost of falls of older people supposes an expense of 35 billion of dollars in the United States [3].

Ageing is associated with several changes that are related to a decrease in physical and mental capacities, which increases fragility and the likelihood of falls in older people [4]. Falls and the resulting disability are particularly common among older people [5]. However, disability severity and fall rates may be reduced through exercise interventions [5]. In this regard, several exercise modalities have shown to be effective improving balance in older people, such as strength training [6,7] and/or resistance training [8]. However, levels of adherence to exercise programs in older people are low [9]. For this reason, there are other physical exercise interventions that could be more effective, cheaper, motivating, and specific for preventing falls, such as the so-called Square Stepping Exercise (SSE) [10].

SSE is a program that consists of performing multiple steps in several directions, on a thin carpet divided into 25 × 25 cm squares. SSE may also be done outdoors or indoors. Thus, this is a great alternative to one-way outdoor walking, which is less beneficial in falls prevention and more unsafe for older people [11]. SSE is an alternative intervention that includes physical exercises that is apparently more effective than walking for improving balance and helping to reduce fall risk factors. Moreover, it is recommended as a health promotion exercise in older people [10].

SSE is designed to improve reaction time during the step as well as to restore balance after a stumble. Furthermore, it involves the activation of agonist and antagonist muscles of the lower limbs. The benefit of SSE also extends beyond fall prevention, improving functional ability, lower limb fitness, and health status of the elderly [10,12]. In fact, a recent systematic review showed that SSE is an effective training system in preventing both fall injuries and fear of falls and improves perceived health status in older adults. Moreover, it indicated that SSE may be applied easily, cost-effectively, and in groups [13].

Fibromyalgia (FM) is a chronic syndrome that affects 3.43% of women worldwide, 3.90% in Europe, and 4.2% in Spain [14]. This syndrome has a considerable functional impact on people who suffer from it, as they present chronic pain problems requiring many social, health, and work resources through comprehensive and continuous care [15]. It is estimated that people with FM represent an annual expense of 11,629.03 euros per patient and year in Spain, costing a total of 4223.02 million euros to Spanish health services, which poses a 279.10-euro cost per inhabitant and year [14]. If we consider that, according to the Ministry of Health of Extremadura, a health expenditure of 1549 euros per inhabitant was made in 2016, the expense on fibromyalgia represents 18% of the total health cost per inhabitant in Extremadura. Therefore, any intervention that may help to reduce these percentages could have a positive impact on reducing the costs of the Extremadura health system.

Falls in people with FM amount to 2.5 per year compared to 0.5 for people without FM [16]. Thus, part of the annual health costs of this syndrome comes from falls. The project that we are presenting attempts to reduce costs associated with falls in this population through balance training with the SSE method, conducted by a professional through video-conferencing (Tele-Square Stepping Exercise; Tele-SSE), improving the balance and preventing falls in women with FM. Reviewing the scientific literature, the SSE program appears to improve balance by preventing falls and decreasing the fear of falling in older adults [13], but no publication had studied the benefits of SSE in people with FM.

Therefore, the main objectives of this project are 1) to investigate the applicability, safety, decrease in the number of falls, and incremental cost-effectiveness ratio of a prevention of falls program through Tele-SSE in women with FM, and 2) to identify key factors for its transfer to the public and private social health system, evaluating the acceptability of Tele-SSE in the agents of the social health system in charge of including Tele-SSE in their services offer.

Additionally, this project has a secondary aim to evaluate the effect of Tele-SSE on balance levels, fear of falling, body composition, physical fitness, quality of life related to health and positive health, pain, disability level, depressive symptoms, and cognitive aspects of participants.

## 2. Materials and Methods 

### 2.1. Study Design

The Consolidated Standards of Reporting Trials Statement (CONSORT) methodology for randomized controlled trials [17], as well as the “Recommendations for conduct, methodological practices, and reporting of cost-effectiveness analyses: second panel on cost-effectiveness in health and medicine” [18], were followed. Due to the nature of the intervention, the double-blind study design is not possible because participants will be aware of their group designation, so a single-blind design will be adopted (all assessments will be conducted by research staff who remain unaware of group assignment). A randomized controlled trial will be conducted. Participants will be randomly 1:1 assigned to the intervention group (Tele-SSE) or the control group (usual care).

### 2.2. Ethics Approval

Ethical approval was provided by the Bioethics and Biosafety Committee at the University of Extremadura (approval number: 79/2018) and this study has been registered in the Clinical Trials Registry provided by the Australian New Zealand Clinical Trial Registry (Request number: 378330; https://www.anzctr.org.au/).

### 2.3. Sample Size

The number of participants was calculated based on the change in quality of life assessed using the 5-level Euroqol-5D questionnaire (EQ-5D-5L). As far as we know, there are no available data on the minimum real change in the EQ-5D-5L in fibromyalgia patients, so we have used a reference of pathology that deals with pain, being this real minimum difference of 0.15 [19]. Therefore, a total of 118 participants (Experimental group; *n* = 59 and Control group; *n* = 59) are needed; accepting alpha and beta risks of 0.05 and 0.2, respectively, in a bilateral contrast, to detect a difference equal to or greater than 0.15 units. It is assumed that the common standard deviation of EQ-5D-5L is 0.26, taking as a reference one of the articles by the principal investigator of this project, which evaluated the health-related quality of life through this questionnaire [20]. A follow-up loss rate of 20% has been estimated. 

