#### 2.7.1. Randomized Trial Main Measures

**Applicability.** The percentage of participants with FM who can perform the proposed training. If any participant is unable to perform the intervention, the cause will be noted.

**Safety.** A record shall be kept about any incidence, injury or problem during the sessions, as well as if possible, the origin of the problem.

**Number of falls in the last year and six months.** Participants will be asked about the number of falls that they have suffered in the past year and six months. The World Health Organization (WHO) definition of falls will be adopted, namely: “Involuntary events that cause the body to lose its balance and find itself on land or on another firm surface that stops it”.

**Incremental cost-effectiveness ratio.** The average cost of the intervention and the effects on health will be calculated for both intervention and control groups. The measurement of health effects is defined as Quality Adjusted Life Years (QALYs), which is calculated by multiplying the life years (life expectancy) with the quality of life of the participants [25]. The health-related quality of life will be evaluated using the EQ-5D-5L questionnaire [26] and this measure will be used for sample calculation. Incremental cost-effectiveness ratio will be calculated by dividing the difference between the average costs of both groups by the difference in mean QALYs gained in both groups. The utilities needed to calculate the QALYs will be computed for each set of health status using the algorithm available on the official website of the EuroQol group (http://www.euroqol.org/). The algorithm used to calculate the EQ-5D-5L utility index will be the “crosswalking” of the EuroQol levels Spanish version. This utility index is comprised between −0.654 (corresponding to the worst state of health and equivalent to 55555) and 1 (perfect state of health and equivalent to 11111).

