## Figures and Tables

**Table 1 ijerph-17-00695-t001:** Proposal progression of Tele-SSE training.

Month	Frequency (Days a Week)	Session Duration	Number of Steps per Sequence	Level of Difficulty
1	3	50 min	4	Beginner 1 and 2
2	3	50 min	6	Intermediate 1
3	3	50 min	6	Intermediate 2
4	3	50 min	8	Intermediate 3
5	3	50 min	8	Advanced 1
6	3	50 min	8	Advanced 2
7	3	50 min	8	Advanced 3
8	3	50 min	8	Advanced 3
9	3	50 min	8	Advanced 3
10	3	50 min	8	Advanced 3
11	3	50 min	8	Advanced 3
12	3	50 min	8	Advanced 3

**Table 2 ijerph-17-00695-t002:** Assessments schedule for both experimental and control group.

Assessment	Baseline	Month 3	Month 6	Month 9	Month 12	Month 13
Applicability	x				x	x
Safety	x				x	x
Number of falls in the last year and six months	x		x		x	x
Incremental cost-effectiveness ratio	x				x	x
Sociodemographic data	x					
Balance	x	x	x	x	x	x
Fall Risk	x	x	x	x	x	x
Fear of falling	x	x	x	x	x	x
Body composition	x	x	x	x	x	x
Physical condition	x	x	x	x	x	x
Pain	x	x	x	x	x	x
Health-related quality of life	x	x	x	x	x	x
Incapacity of fibromyalgia	x	x	x	x	x	x
Depression	x	x	x	x	x	x
Happiness	x	x	x	x	x	x
Physical activity and sedentary behaviors	x	x	x	x	x	x
Clinical global impression	x	x	x	x	x	x

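### The 80% power applies to EQ-5D-5L utility and not to falls or the ICER, and applicability and safety are defined by sessions that only the Tele-SSE arm has

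*Protocol article*

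**What the plan says.** The Abstract lists four outcomes without ranking them: "Primary outcome measures will be: 1) Applicability; 2) safety; 3) annual number of falls; and 4) incremental cost-effectiveness ratio". Section 2.7.1 treats the same four as the main measures.

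The sample size in section 2.3 rests on none of these four directly. It begins: "The number of participants was calculated based on the change in quality of life assessed using the 5-level Euroqol-5D questionnaire (EQ-5D-5L"). The error rates ("accepting alpha and beta risks of 0.05 and 0.2, respectively, in a bilateral contrast"), the target ("to detect a difference equal to or greater than 0.15 units"), the spread ("It is assumed that the common standard deviation of EQ-5D-5L is 0.26") and the attrition ("A follow-up loss rate of 20% has been estimated") all belong to that variable. Section 2.7.1 confirms the choice. Under the ICER it names EQ-5D-5L as the source of the utilities for the QALYs and as the sizing variable. For falls the article gives a background rate of 2.5 a year in fibromyalgia (section 1), but no target reduction, no dispersion and no power.

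Section 2.7.1 defines applicability as the share of participants able to do the training. On safety it says: "A record shall be kept about any incidence, injury or problem during the sessions". Under section 2.6 the control arm continues usual care and has no sessions. Table 2 nevertheless lists applicability and safety at baseline, month 12 and month 13 under the title "Assessments schedule for both experimental and control group". Section 2.8 applies a repeated-measures ANCOVA with a group-by-time term to all main and secondary variables, at p < 0.05.

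**The concern.** There are two separate problems.

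**Power.** Falls are the reason for the trial: the background, the objectives and the discussion all turn on preventing them. The only power statement concerns a different variable. Without a detectable effect for falls, a non-significant falls result cannot be interpreted. It could mean that Tele-SSE does not reduce falls, or that 118 women were too few to show a worthwhile reduction.

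**Applicability and safety.** Two of the four primaries exist in one arm only by definition, yet the schedule and the analysis section treat them as comparative. The planned group comparison cannot be run on them. The article's conclusions look ahead to an intervention shown to be effective and safe. As defined, the safety primary would supply a one-arm record of in-session problems, with no control figure and without injuries that happen at other times.

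**Working it through.** **1. The plan's own figure.** Inputs from section 2.3: difference 0.15, SD 0.26, two-sided alpha 0.05, power 0.80, loss 20%.

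- n per arm = 2 × (1.960 + 0.8416)² × (0.26/0.15)² = 47.16
- allowing for loss: 47.16 / 0.8 = 58.95, so 59 per arm and 118 in total

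The stated figure reproduces. With 47 completers per arm, power for the EQ-5D-5L difference is 79.9%; with all 59 it is 88.0%.

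**2. What this says about the ICER.** The ICER is a difference in mean cost divided by a difference in mean QALYs. Section 2.3 gives no cost difference and no cost variance, so power for the utility difference does not become power for the ratio.

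**3. What this says about falls.** Inputs: control rate 2.5 a year (section 1), one year of follow-up, and 59 × 0.8 = 47.2, taken as 47 completers per arm. The negative-binomial dispersion k is an assumption, because the article gives none. For an unadjusted log rate ratio (RR):

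SE = √{[(1/2.5 + k) + (1/(2.5·RR) + k)] / 47}

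power = Φ(|ln RR| / SE − 1.960)

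| k (assumed) | RR detectable at 80% power | Power, RR 0.5 | Power, RR 0.7 |
|---|---|---|---|
| 0.5 | 0.55 | 89% | 41% |
| 1.0 | 0.48 | 76% | 29% |
| 1.5 | 0.43 | 64% | 23% |

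Worked case, k = 1 and RR = 0.7: SE = √{[(0.4 + 1) + (0.571 + 1)] / 47} = √(2.971/47) = 0.251; |ln 0.7| = 0.357; 0.357/0.251 − 1.960 = −0.54; power 29%.

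How far the assumptions matter:
- With no overdispersion (k = 0), power for RR 0.7 is 70%.
- With all 59 per arm in the same formula, the detectable RR for k = 0.5, 1 and 1.5 becomes 0.59, 0.52 and 0.47.
- Over RR 0.5 to 0.8 and k 0 to 2 with 47 per arm, power runs from about 10% to 99%.

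**4. Applicability and safety, side by side.**

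| Place | What it implies |
|---|---|
| 2.6, control group | No training sessions |
| 2.7.1, applicability | Ability to do the training: Tele-SSE only |
| 2.7.1, safety | Problems within sessions: Tele-SSE only |
| Table 2 | Both measures, both groups, at baseline (before any session), month 12 and month 13 (after the programme ends) |
| 2.8 | Group-by-time comparison of all main variables |

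The first three rows cannot be reconciled with the last two.

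**The case against.** **The sizing basis is disclosed and defensible.** The first sentence of 2.3 names EQ-5D-5L, and 2.7.1 repeats it. Sizing a trial with a cost-utility primary on its utility measure is a reasonable choice. This stands. A reader might infer that the article presents its 80% as power for falls, or that EQ-5D-5L has nothing to do with the primaries. The text supports neither reading. What remains is that nothing is said about falls.

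**The falls figures rest on assumptions.** This also stands. The article gives neither a target rate ratio nor a dispersion, and a halving of falls with low dispersion would be well powered. Section 2.8 adjusts for age and baseline and imputes missing data, which could improve on an unadjusted completers' calculation. The table therefore gives a range for one simple analysis. It does not show that falls cannot succeed.

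**Four unranked primaries do not mean four competing tests.** A reader might infer a large inflation of the false-positive rate. Applicability is a percentage and safety a record, and the ICER is handled in section 2.9 by probabilistic analysis and an acceptability curve. Only falls is clearly a tested primary, and any ordering could sit in an analysis plan that is not shown. Nor does the article call for placing EQ-5D-5L behind falls in a fixed test order. That would make the one outcome with stated power depend on one that may have much less.

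**Some harm data exist in both arms.** A reader might infer that nothing outside the sessions is captured. Table 2 schedules falls and pain for both groups, and section 2.9 costs medication, primary care visits and hospital admissions. None of these, however, belongs to the safety primary as 2.7.1 defines it.

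**Conclusion.** The point holds in a limited form. The 118 is correct for EQ-5D-5L and openly described as such, but its 80% power extends neither to falls nor to the ICER. For falls, 80% power in an unadjusted analysis needs a rate ratio of about 0.55 to 0.43, a reduction of roughly 45% to 57%. This assumes 2.5 falls a year in controls, 47 completers per arm and a dispersion of 0.5 to 1.5; the dispersion is the reviewer's assumption. Lower dispersion or full retention would relax the requirement.

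The contradiction over applicability and safety needs no assumption. As defined they are Tele-SSE-only measures, while Table 2 and section 2.8 treat them as comparative. An in-session record from one arm cannot by itself support a conclusion that the programme is safe. This is the part most worth correcting, because the remedy is cheap and the missing control-arm answers may be hard to recover later.

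**What to change.** 1. In section 2.3, add that no power is claimed for falls or for the ICER. Give the detectable fall rate ratio for 118 participants (about 0.43 to 0.55 under the assumptions above, or a range from the team's own dispersion estimate) and name those assumptions. State that a non-significant falls result will be read from its confidence interval and not as evidence of no effect.
2. Reconcile section 2.7.1, Table 2 and section 2.8: report applicability and in-session events descriptively for the Tele-SSE arm only, and take them out of the group-by-time analysis.
3. Ask both arms the same question about injuries and adverse events since the last visit at each existing follow-up visit (months 3, 6, 9, 12 and 13). Compare the arms by estimates with confidence intervals.

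The cost is changed wording and one extra question per visit, with no added participants, visits or staff. The downside is that the stated power for falls will look less favourable.

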### 2.4. Randomization and Blinding

After baseline assessments, all participants will be randomly assigned to two groups: Experimental (Tele-SSE) or control (usual care). A simple computer-generated randomization sequence will be created before participants are enrolled (1:1) using the computer software Research Randomizer (Version 4.0, Geoffrey C. Urbaniak and Scott Plous, Middletown, CT, USA) (http://www.randomizer.org). The randomization sequence will be made by a member of the research team without clinical participation in the trial. The assignment will be hidden in a password-protected computer file. Although participants will know their group assignment, outcome evaluators and data analysts will be blinded to the assignment.

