### 2.6. Interventions

**Experimental group (Tele-SSE):** The experimental group will receive Tele-SSE training, 3 times a week, for 12 months. They will be given training guidelines through a brochure and all sessions will be tracked through video-conferencing on a mobile phone. Two to six patients will simultaneously perform the exercise in a common place, which will be a room or dependency yielded by each participating association with Internet connection via WIFI. SSE will be carried out on a 250 × 100 cm dimensioned thin carpet, divided into 40 squares of 25 × 25 cm. SSE includes a total of 200 different movement patterns that are classified, based on its difficulty, into three general levels: Beginner, intermediate, and advanced. The beginner level has two sublevels, while the intermediate and advanced levels have 3 sublevels. The proposed intervention will include a progression along with the different levels, which is shown in Table 1. Participants will start by movement patterns like walking and little by little they will make more complex patterns that will require multidirectional movements. Participants should not step on the squares dividing lines. The number of steps patterns and difficulty will monthly increase until the maximum level, where they will be maintained until the end of the intervention.

In all sessions, the SSE expert will phone the group of participants and will indicate the training to be done. Participants will have a brochure detailing the 200 movement patterns, which they can consult while the SSE expert indicates the sequence to follow during the class that day. Before starting the session, the first activity to be carried out will be to remember the last movement pattern executed in the previous session. Once the patients have memorized the pattern, which is expected to be achieved after 4–5 repetitions, based on a previous study [23], they will continue with the session autonomously. At the end of each session, they will contact the SSE expert who will ask them about the session development and will question them about two scales: The rating will be of perceived exertion [24] and level of pain, also recording any incident or problem during the training session.

**Control group:** The control group will continue with the treatment carried out within the public health system (usual care).

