### 2.8. Statistical Analysis

Baseline characteristics of participants will be presented as the mean (standard deviation) for continuous variables and proportions for categorical variables. The normality will be checked using the Kolmogorov-Smirnov test. Then, two types of analyses will be performed: 1) An intention-to-treat analysis including all participants and 2) a per-protocol analysis using only those participants who complete the study.

**Intention-to-treat analysis.** This analysis will include all randomly assigned participants in their corresponding groups. Multiple imputations will be used to impute lost data. The effects of the intervention on the main and secondary variables will be computed using a repeated measures ANCOVA test, adjusted by age and baseline values. Results shall include the Cohen’s *d* effect size (95% confidence interval) and statistical significance for each dependent variable respect to time and its interaction effects (group × time). Statistical significance shall be established at the conventional level of *p* < 0.05. In sensitivity analyses, the data imputation will be made from the baseline patient data and from those participants who completed the study, in order to avoid estimation biases. 

**Analysis by protocol.** Similar analyses than those described above will be carried out, but only using participants who have attended at least 75% of the sessions.

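### Simple 1:1 randomisation does not secure a Tele-SSE training group at associations with few recruits, and the stated ANCOVA would give standard errors that are too small if outcomes correlate within training groups

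*Protocol article*

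**What the plan says.** All references are to the protocol article.

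- **Allocation (2.4).** "A simple computer-generated randomization sequence will be created before participants are enrolled (1:1". No block, stratum or association is named.
- **Delivery (2.6).** "Two to six patients will simultaneously perform the exercise in a common place, which will be a room or dependency yielded by each participating association". Sessions run three times a week for 12 months. Controls continue usual care and have no group.
- **Eligibility (2.5).** Women are expected to try to remain in their own association, so moving a woman elsewhere to fill a group sits badly with the plan.
- **Analysis (2.8).** The effect on main and secondary variables comes from a repeated measures ANCOVA, "adjusted by age and baseline values". No term for association or training group is stated.
- **Sample size (2.3).** 59 women per arm, "accepting alpha and beta risks of 0.05 and 0.2, respectively, in a bilateral contrast", with no allowance for grouping.

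**The concern.** Tele-SSE is delivered to an association-based group, but neither the allocation nor the stated model recognises that unit.

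First, an unrestricted list can leave an association with exactly one Tele-SSE woman, who then has no group to train with, or with none. Delivery as described would fail for the lone woman.

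Second, women in one training group share a room, a call and the same companions for a year. If this makes their outcomes alike, the Tele-SSE mean is less precise than the ANCOVA assumes. Confidence intervals would then be too narrow and the real type I error above 5%. Controls are not grouped, so the effect arises in one arm only.

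**Working it through.** **1. The plan's own sample size.** Section 2.3 gives a two-sided alpha of 0.05, power of 0.80, a difference of 0.15, and this assumption: "the common standard deviation of EQ-5D-5L is 0.26". It also states: "A follow-up loss rate of 20% has been estimated".

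n per arm = 2 × (0.26/0.15)² × (1.960 + 0.842)² = 47.16

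47.16/0.80 = 58.95, so 59 per arm and 118 in total. The stated figure is reproduced, and it assumes independent women.

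**2. Fewer than two Tele-SSE women at an association.** With r recruits and independent 1:1 draws:

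P(0 or 1) = (1 + r)/2^r, and P(exactly 1) = r/2^r

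| Recruits r (assumed) | P(0 or 1) | P(exactly 1) |
|---|---|---|
| 4 | 5/16 = 31% | 4/16 = 25% |
| 6 | 7/64 = 11% | 6/64 = 9.4% |
| 8 | 9/256 = 3.5% | 8/256 = 3.1% |
| 10 | 11/1024 = 1.1% | 10/1024 = 1.0% |

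Over the whole trial, the chance that at least one association has exactly one Tele-SSE woman is 1 − (1 − r/2^r)^k for k associations of r recruits. It is about 86% for 20 associations of 6, 38% for 15 of 8, and 3% for 10 of 12.

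A list drawn with fixed totals of 59 and 59 would barely help. For 4 recruits, P(0) = (59·58·57·56)/(118·117·116·115) = 5.9% and P(1) = 4·59·(59·58·57)/(118·117·116·115) = 25.0%, together 30.9%.

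**3. Arm sizes.** If the draws are independent, P(exactly 59/59) = C(118,59)/2^118 = 7.3%, and P(arms differ by 10 or more) = 41%. Power after 20% loss is Φ(0.15/[0.26·√(1/n₁ + 1/n₂)] − 1.96):

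- 59/59 (47.2 and 47.2 analysed): 80.0%
- 54/64: 79.7%
- 49/69 (39.2 and 55.2 analysed): 78.9%

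**4. Grouping in the Tele-SSE arm only.** For groups of m, the design effect is DE = 1 + (m − 1)·ICC in Tele-SSE and 1 in control.

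- True SE / model SE = √[(DE + 1)/2]
- Real type I error = 2·[1 − Φ(1.96/ratio)]
- Power with the correct SE = Φ(0.15/[0.26·√((DE + 1)/47.2)] − 1.96)
- N to keep 80%: 47.16·(DE + 1)/2 per arm, divided by 0.80, rounded up and doubled

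The documents give no ICC, so every non-zero value is an assumption.

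| m | ICC | DE | SE ratio | Type I error | Power | N for 80% |
|---|---|---|---|---|---|---|
| any | 0 | 1.00 | 1.000 | 5.0% | 80.0% | 118 |
| 2 | 0.01 | 1.01 | 1.002 | 5.1% | 79.8% | 120 |
| 4 | 0.05 | 1.15 | 1.037 | 5.9% | 77% | 128 |
| 6 | 0.10 | 1.50 | 1.118 | 8.0% | 71% | 148 |
| 6 | 0.20 | 2.00 | 1.225 | 11% | 63% | 178 |

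These figures use the plan's two-mean comparison of EQ-5D-5L. They do not credit any gain from baseline adjustment.

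**The case against.** **The standard errors may be sound.** A reader might infer that they are too small as a matter of fact. The documents do not support that: it needs a positive correlation within training groups, and no ICC is given. Table 1 sets the progression by calendar month for everyone. Sections 2.6 and 2.9 refer to a single expert and a single hired person. Pace and instructor, two common sources of between-group variation, therefore look largely standardised. This stands, and it makes a small ICC plausible. The shared room and companions remain, so it does not establish an ICC of zero.

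**The viability risk depends on association size.** Recruits per association are unstated, and from about 10 recruits upward the risk at any one association is about 1% or less. This stands, so the risk is given as a range.

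**The 59/59 split.** A reader might infer that failing to secure equal arms undermines the trial. It does not: 49/69 costs about one point of power. The abstract's two groups of 59 would also fit a list with fixed totals, although section 2.4 states no such restriction.

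**Imbalance between associations.** A reader might infer that it biases the result or shrinks the standard errors. Women are randomised individually, so chance imbalance does not bias the estimate. An association effect shared by both arms does not by itself make the standard errors too small; only the training-group effect in the Tele-SSE arm does.

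**The unseen analysis plan.** It may hold a training-group term. That is possible, but the article states a specific covariate set without one, and it fixes the randomisation method itself.

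**Conclusion.** The point holds in conditional form, in two parts.

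- **Delivery.** Simple allocation does not secure at least two Tele-SSE women at an association with few recruits. The risk runs from 31% (4 recruits) to 1.1% (10 recruits) per association, and the documents do not show where in that range this trial lies.
- **Inference.** The stated ANCOVA treats women who train together as independent. If outcomes correlate within groups, the standard errors will be too small. The size runs from nothing at ICC 0, through 5.9% type I error and 77% power (ICC 0.05, groups of 4), to 8.0% and 71% (ICC 0.10, groups of 6).

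Neither part invalidates the trial. Both leave delivery and error control resting on favourable conditions that the plan does not state, and a modest change to the stated methods would remove that dependence.

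**What to change.** 1. **Allocation.** Replace the simple sequence with permuted blocks of randomly varying size, stratified by association, kept in the same concealed file. Pool very small associations into one stratum. Pooling balances the arms but does not by itself put two Tele-SSE women in the same place, so the protocol should say how delivery is handled there.
2. **Model.** Include association as a factor, using the randomisation strata. Add a partially nested random effect for Tele-SSE training group, or a cluster-robust standard error, with each control as a singleton. The 59 Tele-SSE women form about 15 groups of 4 or 10 of 6, so a small-sample correction is advisable.
3. **Sample size.** Say that the 80% power assumes no within-group correlation, or state an assumed ICC and its consequence (about 128 or 148 women in the two main scenarios above).

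If the list is already in use, adopt items 2 and 3 alone, before unblinding.

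**Cost.** A new list before enrolment and a recorded training-group identifier. Confidence intervals become somewhat wider, and blocking adds some predictability, which varying block sizes limit. Any correlation present already lowers the real power; the fix only makes that visible.
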